### Sample size

The sample size was calculated from SUN’s previous study [16]. The primary outcome was the change of mean defect (MD) value of VF after 8 weeks of treatment compared with baseline. Based on the reference (Sun et al.), the MD value of the treatment group is 2.06 ± 1.73. The MD value of the control group is 0.73 ± 1.93. The difference between the effect values of the treatment period and the control period was 1.43, and the standard deviation of the two periods was 1.93. When a two-tailed test with a test power of 80% and significance level of 5% was applied to the research, 10 cases were calculated [17]. Taking into account of 20% dropout rate, we ultimately identified 12 participants.

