The clinical research is the first application in RP patients with the TpES therapy. With respect to the rationale for carrying out N-of-1 trial rather than RCT, we take the following reasons into consideration.N-of-1 trials are randomized, prospective, controlled, multiple crossover trials in a single patient. Such trials are suitable for the following clinical applications: (1) chronic disease; (2) experimental treatments for rare diseases or with little or no previous research; (3) doubtful about the efficacy and safety of interventions for certain diseases; (4) the intervention has the characteristics of quick onset and short half-life period and the effect can disappear quickly after the intervention is stopped.RP comprises a group of inherited retinal degenerative diseases with a prevalence of 1 in 4000, affecting 2 million persons globally. RP is associated with 3000 mutations in 100 genes. As a rare and chronic disease, adequate recruitment for group trials is not always feasible, informed consent is difficult to obtain, and retention is difficult too. Compared with RCT, the N-of-1 trial has higher power and requires smaller sample sizes.RP is a highly heterogeneous disease. Studies have shown that genotype plays an important role in RP progression. Besides it, there are many other risk factors that may have effect on the progression of RP, such as inheritance patterns, smoking, physical activity, and other demographic and environmental factors. Due to the small cohort sample size and the large clinical heterogeneity of RP patients, it is difficult to obtain high-quality evidence of therapeutic effectiveness. With the consideration of heterogeneity, N-of-1 trial is a more suitable choice.There have been no reports of transpalpebral electrical stimulation for RP treatment up to now. It is an individualized treatment, and the intensity of stimulating current varies with the condition of the retinopathy in each patient. In the trial, patients will perform the treatment by themselves. Therefore, N-of-1 trial has better feasibility than conventional RCT. Moreover, the intervention has the characteristics of quick onset, and the effect can disappear relatively quickly after the intervention is stopped, which make it suitable for N-of-1 trial.

Taken together, based on the characteristics of RP and the intervention method, it is very suitable for the study of RP.

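### The sample size uses a control-group SD from a study with separate groups as the SD of two periods in one patient, so the stated 80% power is not established for this within-patient design

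*Protocol article*

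**What the plan says.** All inputs stand in the Sample size section of the protocol article. The endpoint is given as follows: "The primary outcome was the change of mean defect (MD) value of VF after 8 weeks of treatment compared with baseline". Two groups of an earlier study supply the figures: "the MD value of the treatment group is 2.06 ± 1.73" and "The MD value of the control group is 0.73 ± 1.93". The section then moves from groups to periods: "The difference between the effect values of the treatment period and the control period was 1.43". For the spread, it states that "the standard deviation of the two periods was 1.93". For a "two-tailed test with a test power of 80% and significance level of 5" per cent, "10 cases were calculated", raised to 12 for dropout.

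The Study design section describes three randomised comparisons per patient, each with one 8-week treatment period (A) and one 8-week control period (B). The Primary outcome section schedules the visual field once before treatment and then at the end of every period, so each visit from week 8 to week 40 closes one period and opens the next. The Statistical analysis section treats each patient's pair as an independent trial. It plans a paired t-test for in-group effects, and repeated-measures ANOVA or a mixed model across the three pairs.

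**The concern.** The figure called the SD of the two periods is the control group's SD from a study with separate groups. It is not a pooled value: pooling 1.73 and 1.93 would give 1.83. The planned analyses judge the effect against the variation of A minus B within a patient. That SD depends on the correlation between a patient's two results, and the section gives neither the SD nor the correlation.

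The correlation depends in turn on what baseline means, and the text leaves two readings open. If both changes are taken from enrolment, they share the same starting value. If each is taken from the start of its own period, the visit between the two periods ends one change and starts the other, so its error enters them with opposite signs. At stake is the trial's only statement of power.

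**Working it through.** **Inputs.** From the Sample size section: difference 1.43, SD 1.93, two-sided 5%, power 80%, 10 cases before dropout, group means 2.06 and 0.73. From the Study design section: three pairs per patient. Squared sum of normal quantiles: (1.960 + 0.842)² = 7.849.

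**Reproducing the plan's figure.** For two unpaired groups, n per group = 2 × 7.849 × 1.93² / 1.43² = 28.59. Spread over three cycles, 28.59 / 3 = 9.53, rounded up to 10, which matches the text. Using 1.93 directly as the SD of the paired difference does not match: 7.849 × 1.93² / 1.43² = 14.30 (15 patients) with one pair each, or 14.30 / 3 = 4.77 (5 patients) with three pairs each. The plan's 10 thus corresponds to A and B changes with SD 1.93 each and correlation zero, for which the SD of A − B is 1.93 × √2 = 2.73.

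**What each meaning of baseline would imply.** The documents give no within-patient correlation, so this step rests on an assumption: every visit carries an independent error of equal variance s², patients do not differ in their true effect, and 1.93 is the SD of one before-after change, so that 2s² = 1.93².

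- Enrolment baseline: the enrolment value cancels and A − B is the difference of two visits. Variance 2s², SD 1.93, correlation +0.5.
- As the plan implies: variance 4s², SD 2.73, correlation 0.
- Period-start baseline: for order AB the contrast is (Y1 − Y0) − (Y2 − Y1) = 2·Y1 − Y0 − Y2. Variance 6s², SD 3.34, correlation −0.5.

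**Power with 10 completers and three pairs each.** Normal formula: Φ(difference × √30 / SD − 1.96). With 1.43, the arguments of Φ are 7.832/1.93 − 1.96 = 2.10, 7.832/2.73 − 1.96 = 0.91 and 7.832/3.34 − 1.96 = 0.38. The t column uses 30 pairs (29 df), in line with the rule that each pair counts as an independent trial.

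| Case | SD of A − B | Patients needed, difference 1.43 | Normal power, 1.43 | t power on 30 pairs, 1.43 | Normal power, 1.33 |
|---|---|---|---|---|---|
| Enrolment baseline | 1.93 | 5 | 98% | 97.5% | about 96% |
| Zero correlation (plan) | 2.73 | 10 | 82% | 79% | 76% |
| Period-start baseline | 3.34 | 15 | 65% | 62% | 59% |

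A simulation of the seven visits with random order in each cycle gave 97.5% and 62% for the first and last rows (t on 30 pairs, difference 1.43). At intermediate correlations of +0.25 and −0.25, 8 and 12 patients are needed, and normal power at 10 is 91% and 73%.

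**The last column.** The quoted means differ by 2.06 − 0.73 = 1.33, not 1.43. With 1.33 the plan's own formula gives 2 × 7.849 × 1.93² / (3 × 1.33²) = 11.02, that is 12 before dropout.

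**Sensitivity to the assumption.** If MD drifted as a random walk, successive period-start changes would be uncorrelated and the zero-correlation row (82% or 79%) would apply to that baseline. If the true effect varied between patients with an SD of 1.0 (an assumed value), a t-test on 10 patient means would have 77% power with the enrolment baseline and 46% with the period-start baseline.

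**The case against.** The strongest objection is that the formula suits this design. It credits three cycles per patient, and it would be correct if 1.93 were a within-patient SD. This stands in part. A reader might infer that the plan ignores the repeated design altogether, and the reproduced figure shows that it does not. What is missing is a basis for treating 1.93 as a within-patient SD, because the section itself shows that the number comes from a separate control group.

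The second objection is that the 98% and 65% belong to an assumed error model. This also stands. A reader might infer that 80% is wrong under either meaning of baseline, or that the trial is underpowered. The documents support neither reading: random-walk drift brings the period-start case back to about 80%, and variation in effect between patients can bring the enrolment case down to 77%. The Discussion itself calls RP highly heterogeneous, so some variation in effect is plausible.

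A reader might prefer one mean per patient and 9 df, which gives 95%, 72% and 55% for the three rows of the table at 1.43. That is not the analysis described, which counts each pair as an independent trial.

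A reader might also infer, from the Discussion's statement that "There have been no reports of transpalpebral electrical stimulation for RP treatment up to now", that the borrowed figures come from a different treatment. The Sample size section does not say what the earlier study treated, and that study is not shown, so no such claim is made here.

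Finally, the article condenses a fuller protocol, which may define baseline. That does not answer the point: the article states its inputs and result, gives one input a label that its own preceding sentence contradicts, and the result follows from those inputs.

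**Conclusion.** The point holds in a limited form. The calculation reproduces, but it rests on a control-group SD relabelled as the SD of two periods and on an unstated zero correlation between a patient's A and B changes. The SD of the trial's own contrast does not enter it, so the 80% is not established for this design.

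The size is illustrative. With independent, equal visit errors and no variation in effect between patients, the choice of baseline alone moves power at 10 completers from about 65% to 98% at a difference of 1.43, or from about 59% to 96% at the 1.33 that the quoted means give. The direction of the error is unknown. Reading the ± figures as changes from baseline is itself an inference, from the sentence that precedes them.

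**What to change.** - Define the primary contrast as MD at the end of A minus MD at the end of B within the same cycle. The enrolment value then cancels, and the ambiguity over baseline disappears.
- Restate power for the planned number from an SD of that within-patient difference or, failing that, over a stated range of correlations, and say what is assumed about variation in effect between patients.
- Use a difference that agrees with the quoted means (1.33), or correct the means.
- Justify 1.93 as a within-patient figure, or say plainly that it comes from separate groups. The Introduction mentions the authors' own observations of the treatment in RP patients; if usable, they are a natural check.
- Settle the dropout step in the same rewrite: 10 × 1.2 = 12, whereas 10 / 0.8 = 12.5 rounds up to 13, and 20% dropout from 12 leaves 9.6 completers.

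The cost is one rewritten paragraph and a changed power statement. The schedule of visits already supplies the measurements that the contrast needs.

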### Outcome measurements

When the participants are enrolled, their demographic data, such as name, gender, age, ethnicity, and contact details, are recorded. Medical histories are also recorded including current and prior diagnosis, course of RP disease, and any previous treatment.

#### Primary outcome

In this study, the primary outcome is VF [18]. Quantitative index of VF, including MD, mean sensitivity (MS), and square root of loss variance (sLV), will be examined by OCTOPUS automatic perimetry. The 32-test procedure is suitable for visual acuity greater than 0.3, and the LVC test procedure is suitable for visual acuity less than 0.3. The examination time points are before treatment and then at week 8, week 16, week 24, week 32, week 40, and week 48 (Table 1).

**Table 1 Tab1:** Schedule of enrolment, intervention, assessment

Item	Screening	Observation period						
		Cycle 1		Cycle 2		Cycle 3		Closeout
Time point	Enrollment	Weeks 1–8	Weeks 9–16	Weeks 17–24	Weeks 25–32	Weeks 33–40	Weeks 41–48	
Demographic data	√							
Medical history	√							
Informed consent form	√							
BCVA	√	√	√	√	√	√	√	
VF	√	√	√	√	√	√	√	
OCT	√	√	√	√	√	√	√	
FAF	√	√	√	√	√	√	√	
ERG	√	√	√	√	√	√	√	
NEI VFQ-25	√	√	√	√	√	√	√	
Adverse event		√	√	√	√	√	√	

√ Items that must be performed

*BCVA* Best corrected visual acuity, *VF* Visual field, *OCT* Optical coherence tomography, *FAF* Fundus autofluorescence, *ERG* Electroretinogram, *NEI VFQ-25* 25-Item National Eye Institute Visual Function questionnaire

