### Statistical analysis

Statistical analysis will be performed by Statistical Package for the Social Sciences (SPSS) for version 25.0. Descriptive statistics will be used to analyze demographic characteristics of participants, including age and gender. Continuous variables will be presented as mean ± standard deviation. The primary and secondary outcomes will be analyzed using the full analysis set. Each patient’s paired trial is treated as an independent trial. For the in-group effects, the paired *t*-test is used for the data with normal distribution, and the Wilcoxon rank sum test is used for the data with non-normal distribution. For the intergroup effect, three pairs of data with normal distribution will be used with repeatability measure ANOVA test, and linear mixed-effects model will be used with non-normal distribution. For missing values, we will use a mixed-effects model for repeated measures. The *P* (2-tailed) value with threshold less than 0.05 will be considered statistically significant.

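### The primary outcome is defined in two ways, as change in MD alone and as visual field with three unranked indices, so the 5% level is not tied to one test

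*Protocol article*

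**What the plan says.** Four sections of the protocol article bear on this.

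- **Sample size.** One index is named: "The primary outcome was the change of mean defect (MD) value of VF after 8 weeks of treatment compared with baseline". The planning figures are for MD only, and the result is given as "When a two-tailed test with a test power of 80% and significance level of 5% was applied to the research, 10 cases were calculated".
- **Primary outcome.** The outcome is declared to be visual field, without a single index. The next sentence reads "Quantitative index of VF, including MD, mean sensitivity (MS), and square root of loss variance (sLV), will be examined by OCTOPUS automatic perimetry". There is no order among the three and no rule for what counts as success. The Methods part of the abstract is equally general: its main outcome is the visual field assessment.
- **Secondary outcomes.** The list is BCVA, OCT, FAF, ERG and vision-related quality of life. Neither MS nor sLV appears.
- **Statistical analysis.** Primary and secondary outcomes are analysed in the full analysis set. The only decision rule is that a two-tailed P "value with threshold less than 0.05 will be considered statistically significant".

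**The concern.** A confirmatory 5% level belongs to a stated hypothesis. Here a reader cannot tell from the text whether the primary hypothesis concerns MD or a family of three indices. Because MS and sLV sit under the primary heading and are absent from the secondary list, the Primary outcome section does not read naturally as MD with two supporting measures.

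With the definition left open, the index that carries the conclusion could be settled after the results are known. A significant sLV beside a null MD could be reported as a positive primary result under one section and a negative one under the other. In a trial of 12 participants that aims to supply high-quality evidence for clinical use, the main claim should not depend on which section is followed.

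**Working it through.** **1. What the sample size covers.** The inputs, from the Sample size section, are a difference of 1.43 ("The difference between the effect values of the treatment period and the control period was 1.43"), an SD of 1.93 ("the standard deviation of the two periods was 1.93"), two-sided alpha 0.05 and power 80%.

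Two-sample normal formula: n per period = 2 × (1.960 + 0.842)² × 1.93² / 1.43² = 2 × 7.85 × 3.725 / 2.045 = 28.6, so 29.

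Divided by the three crossover pairs per patient: 29 / 3 = 9.67, so 10. This matches the stated 10 cases. The document does not state the division. It is inferred from the design and from the plan to treat each pair as an independent trial. Without it, the same inputs give 15 (paired z), 17 (paired t) or 29 per arm (two-sample). The stated 12 then follows as 10 × 1.2 = 12.

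The sizing therefore rests on one test, of MD, at two-sided 5%.

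**2. False-positive rate under each reading.** Each single test is taken to hold its own 5% level.

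- *MD alone is primary:* one test, 5%.
- *All three must be significant:* the chance that all three reject cannot exceed the chance that any one of them does, so at most 5%.
- *Any one of the three suffices:* if independent, 1 − 0.95³ = 1 − 0.857 = 0.143, or 14.3%. Positive correlation lowers this.

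For the any-one reading, three correlated two-sided t-tests were simulated, with 100,000 runs per case. The two figures in each range come from n = 12 and n = 36. All correlations are assumed.

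| MD–MS correlation | sLV with each | Chance of at least one P < 0.05 |
|---|---|---|
| 0 | 0 | 14.1–14.3% |
| 0.5 | 0.5 | 12.6–12.9% |
| 0.8 | 0.5 | 11.6–11.8% |
| 0.95 | 0.3 | 10.9–11.0% |
| 0.95 | 0.5 | 10.3–10.4% |
| 0.99 | 0.3 | 10.0–10.2% |
| 0.99 | 0.8 | 8.3–8.6% |

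As a limiting case, if MD and MS are fully redundant and sLV is independent, there are in effect two tests: 1 − 0.95² = 9.75%.

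MD and MS both summarise the same examination, so the lower rows are the more plausible ones: roughly 8 to 10%, and 11% in one of them. The independence figure serves as an upper limit.

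**3. Cost of keeping three primary indices.** With Bonferroni at 0.05/3 = 0.0167, and the MD inputs applied to each index, the formula in step 1 gives 2 × (2.394 + 0.842)² × 1.93² / 1.43² = 38.1, so 39 per period. Then 39 / 3 = 13 evaluable patients. Enrolment becomes 13 × 1.2 = 15.6, so 16, or 13 / 0.8 = 16.25, so 17. Kept at 10 evaluable patients (30 pairs), power falls from 81.8% to 68.3%.

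**The case against.** The strongest reply is that the primary outcome is already settled. The Sample size section names the MD change, so the three indices in the Primary outcome section only describe what the perimeter reports, much as the Secondary outcomes section lists five ERG indexes. On that reading there is one primary test and no inflation. The reply also notes that an index hierarchy or multiplicity procedure is often left to the full protocol or analysis plan, neither of which is shown.

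Much of this stands. A reader might infer that the trial has three primary outcomes, each tested at 0.05, and that its primary error rate is therefore above 5%. The document does not support that. It nowhere says that one significant index is enough, and a general threshold is not a decision to forgo adjustment. The absence of a multiplicity procedure is not itself a fault here. The 14.3% figure would also mislead as a headline, because three indices from one examination are unlikely to be independent.

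The reply does not remove the contradiction. The two sections define the primary outcome differently, and an analysis plan would have to choose between them. The MD sentence is also in the past tense and directly follows a reference to a previous study, so it could be read as describing that study's outcome. It is not firm enough to override the section headed Primary outcome.

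**Conclusion.** The finding is an internal inconsistency: MD change in the Sample size section, and visual field with three unranked indices in the Primary outcome section. That much rests on the text alone.

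The effect on the error rate is conditional. It arises only under an any-one-index rule, which the document neither states nor excludes, and its size of about 8 to 10%, with a ceiling near 14%, depends on assumed correlations. The contradiction should still be resolved, because it leaves the choice of index open until results are seen and the planned sample supports only one test at 5%.

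**What to change.** In the Primary outcome section, state that the single primary outcome is the change in MD at the end of each 8-week period, tested at two-sided 0.05. Move MS and sLV to the Secondary outcomes section and say that they carry no confirmatory claim. Use the same wording in the abstract.

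This costs a few sentences. It matches the Sample size section, leaves the sample-size basis as it is and needs no additional measurements. It should be made and dated before outcome data are analysed. That matters here because the Discussion says analysis need not wait for the end of the trial.

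If the sponsor prefers to keep three primary indices, the plan should state the success rule. Unless all three must be significant, it should also state a multiplicity procedure and resize the trial; the Bonferroni figures above show the order of the cost.

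A separate check is needed in the same section: the quoted means differ by 2.06 − 0.73 = 1.33, not the 1.43 used. That does not affect the point made here.

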#### Secondary outcomes

Secondary outcomes include BCVA, optical coherence tomography (OCT), fundus autofluorescence (FAF), electroretinogram (ERG) and vision-related quality of life (VRQoL). The examination time points are before treatment and then at week 8, week 16, week 24, week 32, week 40, and week 48. BCVA will be examined by ETDRS visual acuity chart [19]. ERG includes five indexes, rod response, maximal combined rod-cone response, scotopic oscillatory potentials, cone response, and photopic 30 Hz flicker [20]. OCT measures the thickness of macular fovea [21]. Heidelberg ultra-wide angle photography technique will be used to examine the fundus images under the natural pupil [19]. The VRQoL is evaluated with NEI VFQ-25 questionnaire [22]. The NEI VFQ-25 consists of 26 items that address 12 aspects of daily living as follows: general health, general vision, near vision, distance vision, driving, peripheral vision, color vision, ocular pain, role limitation, dependency, social function, and mental health. Under the guidance of a research assistant, the questionnaire is self-administered by the study participants themselves.

### Safety evaluation

A standard examination will be performed to evaluate treatment safety at the beginning and the end of each period. The most common minor adverse events (AEs) from the ES procedures are skin allergies, headache, and dizziness. Other AEs such as unusual or uncomfortable sensations will be reported at the end of daily stimulation sessions.

### Statistical analysis

Statistical analysis will be performed by Statistical Package for the Social Sciences (SPSS) for version 25.0. Descriptive statistics will be used to analyze demographic characteristics of participants, including age and gender. Continuous variables will be presented as mean ± standard deviation. The primary and secondary outcomes will be analyzed using the full analysis set. Each patient’s paired trial is treated as an independent trial. For the in-group effects, the paired *t*-test is used for the data with normal distribution, and the Wilcoxon rank sum test is used for the data with non-normal distribution. For the intergroup effect, three pairs of data with normal distribution will be used with repeatability measure ANOVA test, and linear mixed-effects model will be used with non-normal distribution. For missing values, we will use a mixed-effects model for repeated measures. The *P* (2-tailed) value with threshold less than 0.05 will be considered statistically significant.

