### Study design

This is a prospective, comparative, and single-blind N-of-1 trial, which includes 3 crossover comparisons. Each comparison includes an 8-week treatment period (A) and an 8-week control period (B). According to the random number generated by Strategic Applications Software (SAS), the random arrangement of AB or BA is presented in each cycle (Fig. 1).

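### The statistical analysis section appears to count one patient's three treatment–control pairs as independent units; if the effect of TpES varies between patients, the standard error of the average effect is too small

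*Protocol article*

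**What the plan says.** Four places in the protocol article bear on this.

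- Study design: each patient's N-of-1 trial is one "which includes 3 crossover comparisons", each made up of an 8-week treatment period (A) and an 8-week control period (B). Twelve patients therefore give up to 36 A–B pairs.
- Statistical analysis: each patient's "paired trial is treated as an independent trial". The next sentence reads "For the in-group effects, the paired *t*-test is used for the data with normal distribution", with a Wilcoxon test otherwise. For the intergroup effect, "three pairs of data with normal distribution will be used with repeatability measure ANOVA test", and a "linear mixed-effects model will be used with non-normal distribution". Neither the subject factor nor the random effects are named.
- Sample size: from a difference of 1.43, an SD of 1.93 and a "two-tailed test with a test power of 80% and significance level of 5"%, the article arrives at 10 cases, raised to 12 for 20% dropout.
- Discussion: "RP is a highly heterogeneous disease". This is offered as a reason for choosing the N-of-1 design.

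**The concern.** The three A–B differences of one patient share whatever true effect TpES has in that patient. If that effect differs between patients, the three differences are correlated, and three pairs from one person carry less information about the average effect than three pairs from three people. A test that treats all pairs as independent leaves this between-patient component out of the standard error.

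The stated aim is evidence for clinical application, which is a claim about RP patients in general and not only about the 12 enrolled. For that claim the between-patient component belongs in the standard error.

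The section also points in two directions. An analyst could follow the independence sentence and the paired t-test, or the repeated-measures ANOVA or mixed model, and obtain different P values for the primary visual field comparison. Each could be defended from the text.

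**Working it through.** **Step 1: reproduce the 10 cases.** Inputs from Sample size: difference 1.43, SD 1.93, two-sided 5%, power 80%.

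2 × (1.960 + 0.842)² × 1.93² / 1.43² = 28.59

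28.59 / 3 pairs per patient = 9.53, rounded up to 10.

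The article does not state the division by 3. The other two-sided calculations tried do not give 10: a paired z formula gives 14.3 (15), a paired t calculation 17, and two independent groups 29 to 30 per group. The stated figure is thus reached when three pairs from one patient count as three replicates.

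**Step 2: assumptions.** The article gives no variance components, so two assumptions are needed.

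- The SD of one A–B difference is 1.93 × √2 = 2.73, that is, no within-patient correlation between periods. This matches the factor 2 in step 1.
- ICC is the share of that variance due to true differences between patients in the treatment effect. It is shown over a range.

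**Step 3: variance and error rate.** With three pairs per patient, the true variance of the overall mean difference is 1 + 2 × ICC times the variance under independence. A nominal 5% test of zero average effect then has true two-sided error 2 × [1 − Φ(1.96 / √(1 + 2 × ICC))]. The simulation used 12 patients, 3 pairs each and 100,000 runs per setting.

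| ICC | 1 + 2 × ICC | 1.96 / √(1 + 2 × ICC) | Error, formula | Error, simulated |
|---|---|---|---|---|
| 0 | 1.0 | 1.96 | 5.0% | 5.0% |
| 0.1 | 1.2 | 1.79 | 7.4% | 7.3% |
| 0.3 | 1.6 | 1.55 | 12.1% | 12.2% |
| 0.5 | 2.0 | 1.39 | 16.6% | 17.2% |

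A t-test on the 12 patient means held about 5% throughout.

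**Step 4: interval width.** Mean simulated 95% widths, pairs as independent (35 df) against patient as unit (11 df):

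- ICC 0: 1.83 against 1.96, ratio 1.07 (a cost in degrees of freedom only)
- ICC 0.3: 1.82 against 2.48, ratio 1.36
- ICC 0.5: 1.80 against 2.77, ratio 1.54

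**Step 5: power with the patient as unit.** Noncentral t with 11 df, 12 completers, variance of the mean = 2.73² × [ICC + (1 − ICC)/3] / 12. The standard errors are 0.455, 0.538 and 0.643 at ICC 0, 0.2 and 0.5.

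| Difference | ICC 0 | ICC 0.2 | ICC 0.5 |
|---|---|---|---|
| 1.43 (stated) | 82% | 68% | 53% |
| 1.33 (2.06 − 0.73, the two means in Sample size) | 76% | 62% | 47% |

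The second row is shown because the stated difference does not match the means beside it; that is a separate discrepancy. If only the 10 planned completers remain, simulated power at 1.43 is 73%, 58% and 44%.

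**The case against.** The strongest reply is that the sentence means something harmless: each patient's whole N-of-1 series is a trial independent of the other patients' series. The article elsewhere calls the replicates comparisons, cycles or pairs, and it nowhere mentions 36 units. This reading cannot be excluded. The word paired, the t-test that follows and the sample size arithmetic favour the other reading, and the sentence needs rewording under either.

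Second, the intergroup effect is assigned to repeated-measures ANOVA or a mixed model. With the patient as subject and the treatment effect tested against its variation between patients, either would be close to the remedy below. That stands, so a reader should not infer that the primary P value will certainly come from pooled pairs. The article does not settle it, and a random patient intercept alone would not allow for varying response.

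Third, a reader might infer that the plan produces false positives even when TpES does nothing. It does not. Stable differences between patients cancel in A minus B. With no effect in any patient the ICC is 0 and the error stays at 5%. The inflation concerns only the hypothesis that the average effect is zero while individual effects differ around it.

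Fourth, the heterogeneity described in the Discussion is mainly in genotype, progression and current intensity, not in the A–B effect. It makes varying response plausible but gives it no size.

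**Conclusion.** The point holds in a conditional form. On the better supported reading, the independence rule treats three pairs from one patient as three units and conflicts with the clustered methods named in the same section. If the effect varies between patients, the nominal 5% test of zero average effect runs at about 7% to 17% for ICC 0.1 to 0.5, and a correct interval is about 36% and 54% wider at ICC 0.3 and 0.5. The 80% power goal is met with 12 completers at the stated difference only if the effect is close to constant across patients.

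These sizes rest on the assumed ICC and on uncorrelated periods; the article supports neither with a figure. The division by 3 in the sample size fits the numbers but is not stated, so it should not be presented as the sponsor's documented method.

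**What to change.** Delete the independence sentence and name the patient as the unit for the primary A–B comparison. Use one mixed model with a random patient intercept and a random patient-by-treatment effect. A one-sample t-test on patient-mean differences is equivalent only with complete, balanced data, which the 20% dropout allowance makes unlikely.

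In Sample size, state how 10 was obtained and give the power as conditional on the between-patient variance of the effect, over a range such as the one above.

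The change is to wording and analysis only, with no new visits or measurements. The downside is a wider interval and a lower stated power. It should be made before outcome data are seen, since a choice between the two analyses made afterwards would not be credible.
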